## Methods - testing the hypothesis

### Design and setting

This study is a multi-centred single blind, randomised, control trial with parallel design.

Subjects will be recruited from the neurological rehabilitation department of 3 participating Swiss hospitals: Felix Platter Spital Basel, Kantonspital Luzern Neurorehabiltaton and Reha Clinic Zurzach. Each department is a dedicated unit specialising in the rehabilitation of post acute neurological patients. Ethical approval has been obtained from the following cantonal ethics committees: Basel (Ethikkommission Beider Basel), Luzern (Ethikkommission Kanton Luzern), Aargau (Ethikkommission Kanton Aargau).

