### Sample size and power calculation

In order to detect a clinically significant difference in the primary outcome measure of "Timed up and go" of 10 sec (from a likely range of 10-40 sec), with a probability of 80% at a two sided 5% significance level a total of 116 patients (58 per group) must enter the study. This calculation was performed assuming a SD of the timed up and go of 19 sec [52]. Since there are indications that the distributions of the primary endpoint variable is skewed, the use of a nonparametric test should increase the actual power. To allow for drop-outs 60 participants per intervention will be recruited.

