### Statistical methods

The primary analysis will be performed in an intention-to-treat fashion, i.e. all subjects who where randomised and have at least a Timed Up and Go assessment before start of therapy will be included in all analyses. In the primary analysis, missing values will be replaced by the last available value. If no value under or after treatment is available, the value measured before start of therapy will be used.

The primary analysis will be performed on the Timed Up and Go after 5 weeks of therapy. A nonparametric two sample Wilcoxon-Mann-Whitney test will be performed. Significance levels will be 5%. As robustness analyses, an analysis of covariance will be performed with the value before start of therapy as covariate and centre and therapy as factors. 95% CI's will be calculated based on this analysis. Descriptive statistics for all data will be presented. For continuous data, this will include the change from pre-therapy values. Pre-therapy values will be compared between groups to identify relevant co-variables.

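### The primary Wilcoxon test on 5-week TUG leaves out the baseline TUG that every analysed patient has, and the only 95% CI comes from a different model: valid, but inefficient and hard to report

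*Protocol article*

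**What the plan says.** Everything decisive stands in the protocol article under Statistical methods.

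- Endpoint: "The primary analysis will be performed on the Timed Up and Go after 5 weeks of therapy". This is the final value. Change from pre-therapy appears only among the descriptive statistics.
- Primary test: "A nonparametric two sample Wilcoxon-Mann-Whitney test will be performed". No covariate or stratum is named.
- Adjusted model, labelled a robustness analysis: "an analysis of covariance will be performed with the value before start of therapy as covariate and centre and therapy as factors". No transformation is stated.
- Interval: "95% CI's will be calculated based on this analysis", that is, on the ANCOVA.
- Analysis set: randomised subjects who "have at least a Timed Up and Go assessment before start of therapy will be included in all analyses".

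Design and setting names three recruiting hospitals. Sample size and power calculation sizes the trial for 10 s and adds: "This calculation was performed assuming a SD of the timed up and go of 19 sec". That section expects a skewed endpoint and argues that a nonparametric test should therefore gain power.

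**The concern.** The analysis set requires a pre-therapy TUG, so the covariate is present for every analysed patient. The primary test nevertheless leaves differences in starting level in its noise. The protocol's power argument for a nonparametric test compares it with an unadjusted comparison of means. It does not address what baseline adjustment would add.

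The second issue is reporting. The decisive p-value comes from unadjusted ranks, while the only interval describes a mean difference adjusted for baseline and centre. A reader could see a non-significant primary test beside a CI that excludes zero, or the reverse, with no estimate belonging to the test that decides the trial.

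**Working it through.** **Inputs from the protocol.** Difference 10 s, SD 19 s, two-sided 5%, power 80%, 58 per group.

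**Assumptions.** The correlation r between baseline and 5-week TUG is not given; 0.3 to 0.8 is used. Skewed data are modelled as lognormal with mean 30 s and SD 19 s (the mean is assumed). Any centre effect is unknown, so the figures below reflect baseline adjustment only.

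**1. Reproduce the stated size.** Normal approximation: n per arm = 2(1.96 + 0.842)² × (19/10)² = 2 × 7.85 × 3.61 = 56.7, so 57. The two-sample t-test gives 57.6, so 58 per arm and 116 in total, as stated (power 0.802).

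**2. Planned test under normality.** The Wilcoxon test has relative efficiency 0.955 against the t-test, so 58 patients per arm count as 58 × 0.955 = 55.4. Power is then 0.79. Simulation gave 0.78-0.79.

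**3. Baseline adjustment under normality.** Residual SD = 19√(1 − r²). Power = Φ(10 / (residual SD × √(2/58)) − 1.96).

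| r (assumed) | Residual SD (s) | Power at 58 per arm | n per arm for 80% |
|---|---|---|---|
| 0.3 | 18.12 | 84% | 52 |
| 0.5 | 16.45 | 91% | 43 |
| 0.6 | 15.20 | 94% | 37 |
| 0.7 | 13.57 | 98% | 29 |
| 0.8 | 11.40 | >99% | 21 |

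Example for r = 0.5: 16.45 × √(2/58) = 3.055; 10/3.055 − 1.96 = 1.31; Φ(1.31) = 0.905.

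**4. Skewed data, simulated at 58 per arm, r = 0.3 to 0.8.**

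| True effect | Wilcoxon | Log or rank ANCOVA | Wilcoxon and ANCOVA on seconds differ on significance |
|---|---|---|---|
| 10 s mean difference (ratio 20/30) | 95-96% | 97-100% | 4-6% |
| 10 s constant shift | about 96% | rank: 98-100% at r = 0.5 to 0.8 | 5-14% |
| 7.5 s mean difference (ratio 0.75) | about 73% | 77-99% | 16-25% |

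The gain is about 1-5 points at 10 s and about 4-25 points at 7.5 s. Null rejection stayed near 5% for every method. The log model was not run for the constant shift.

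**5. ANCOVA on seconds as the alternative.** Under skew with a 10 s shift it reached 83-89% at r = 0.3 to 0.5, against 96% for Wilcoxon. It is therefore not a safe replacement.

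**The case against.** The case for leaving the plan alone is substantial, and much of it stands. The Wilcoxon test controls type I error, the sample size reproduces, and if TUG is as skewed as expected the test exceeds its 80% target at 10 s. Choosing a nonparametric test because of skew is reasoned, and step 5 supports it against an untransformed ANCOVA. Power is lost only relative to another method, by an amount that rests on an unstated correlation.

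Four stronger readings are tempting, and the document does not support them.

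- *No rule says which result prevails.* The protocol names the Wilcoxon test as primary and introduces the other model with "As robustness analyses, an analysis of covariance will be performed with the value before start of therapy as covariate". The hierarchy is fixed.
- *The two results can point in opposite directions.* They can differ on significance, as any primary and sensitivity pair can. In 30,000 simulated trials they were never both significant with opposite signs.
- *Baseline and centre are ignored.* They are left out of the primary test only.
- *An SD of 19 s is impossible for a 10-40 s range.* The bound of (40 − 10)/2 = 15 s applies to hard limits. The protocol calls this range likely, so the bound does not bind.

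That the ANCOVA runs on seconds is also an inference from silence; a fuller analysis plan may specify a transformation. This tempers the skew criticism of the CI but not the other two points: the primary test is unadjusted, and the interval comes from another model.

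**Conclusion.** The point holds as a should-fix on efficiency and reporting. No error of validity, type I error or sample size is shown.

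The size depends on what is true. At the design difference of 10 s, adjustment lifts power from 78-79% to 84% or more under normality. Under the lognormal model, where Wilcoxon already has about 95%, it adds only a few points. The gain matters most if the true effect is smaller than planned: at 7.5 s it ranges from about 4 to 25 points as r rises from 0.3 to 0.8. The disagreement rates for skewed data assume that the ANCOVA is run on seconds. All these figures rest on the assumed correlation and mean, and none of them quantifies the contribution of centre.

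**What to change.** Before unblinding, make the primary test adjusted for baseline TUG and centre on a scale suited to skew. Two forms would serve.

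- ANCOVA on log(TUG) with log baseline TUG, centre and therapy, reporting the ratio of geometric means, its 95% CI and the p-value from that one model. This removes the mismatch completely.
- Rank ANCOVA with baseline TUG and centre. This keeps the protocol's nonparametric choice and recovers most of the same power, but it does not itself yield an interval in seconds, so the plan must name which estimate and CI accompany it.

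Keep the unadjusted Wilcoxon test as a sensitivity analysis, with a Hodges-Lehmann estimate and CI. If Wilcoxon must stay primary, that estimate and CI alone would cure the reporting mismatch, though not the loss of power. Do not simply promote the ANCOVA on seconds.

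The cost is small: the variables are already collected and recruitment of 120 need not change. With the log model, the 10 s target must also be expressed as a ratio (for example 20/30 = 0.67 if the control mean were 30 s) and the power statement reworded to match.

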## Discussion - implications of the hypothesis

Various forms of walking aids are commonly used in post stroke rehabilitation although the long term effects have been sparsely researched. In order to ensure the positive effect of these treatments and to enable evidence based practice, these interventions should be clinically researched.

Early walking is an important aim of stroke rehabilitation for many reasons including the psychological well-being of the patient, to prevent loss of cardiovascular fitness or the development of secondary musculoskeletal problems. This study questions whether canes are the optimal walking aid to enable early independent walking as their use inhibits rather than stimulates activity of the hemiplegic musculature and reduces the use of automatic balance responses contrary to the aims of rehabilitation. A possible alternative to cane use was recently tested by the authors in whom the immediate effects of TheraTogs were to significantly improve hip abductor muscle activity compared to cane walking or walking without walking aids [38].

The rate of recovery of all impairments after stroke is greatest in the first few weeks and slows down after two to three months. Kwakkel et al. discussed an early window during which rehabilitation has the most long term impact [17]. The potential negative or positive effects of walking aids may therefore be particularly significant in this early stage. To our knowledge no studies have investigated this question before. The results of this study may have important clinical significance and could be used in the development of guidelines for gait rehabilitation following stroke.
